### **1.8.2. SECONDARY OUTCOMES**

The secondary outcomes are:

- Biochemical success (PASO criteria, Section 1.9) at 6 months, analysed as a 3-level categorical variable (complete, partial, none);
- Clinical success (PASO criteria, Section 1.9) at 6 months, analysed as a 3-level categorical variable (complete, partial, none);
- Modified clinical success (based on PASO criteria, Section 1.9) at 6 months, analysed as a 3-level categorical variable (complete, partial, none);
- Change in serum potassium from baseline to 6 months;
- Changes in  $ARR_{\text{activity}}$  and  $ARR_{\text{mass}}$  from baseline to 6 months;
- Changes in home SBP and DBP from baseline to 6 months;
- Changes in clinic SBP and DBP from baseline to 6 months;

- Change in defined daily doses of antihypertensive drugs from baseline to 6 months;
- Change in number of antihypertensive drugs from baseline to 6 months;
- Change in number of classes of antihypertensive drugs from baseline to 6 months;
- Change in blood levels of Troponin, Brain Natriuretic Peptide from baseline to 6 months;
- Changes in cardiac MRI measures of heart structure, anatomy and blood flow from baseline to 6 months;
- Changes in quality of life from baseline to 6 months.

### **1.9. PASO CRITERIA**

The following criteria will be used to define cure of hypertension, from the PASO criteria [Williams TA, et al. Lancet Diabetes Endocrinol. 2017 Sep; 5(9): 689-699], six months post-adrenalectomy.

#### **Clinical success:**

- Complete clinical success

Complete clinical success will be declared when both (a) and (b) have occurred:

(a) Normalisation of BP, defined as SBP<135 and DBP<85 mmHg on home BP; if home BP not available, then defined as SBP<140 and DBP<90 mmHg on clinic BP

(b) Not taking any antihypertensive medications

- Partial clinical success

Partial clinical success will be declared when the criteria for complete success are not met, and either (a) or (b) has occurred:

(a) reduction in BP, with no increase in antihypertensive medication, i.e. both of (i) and (ii) have occurred:

(i) BP has reduced, or has normalised, since baseline (based on home BP if available, otherwise based on clinic BP); reduction in BP defined as

- (1) a reduction in SBP of  $\geq 20$ mmHg, or
- (2) a reduction in DBP of  $\geq 10$ mmHg, with a change in SBP of  $< 20$ mmHg

(ii) the defined daily dose of antihypertensive medication being used is <150% of baseline

(b) reduction in antihypertensive medication, with no increase in BP, i.e.

(i) BP is unchanged since baseline (based on home BP if available, otherwise based on clinic BP); unchanged BP defined as

- (1) a change in SBP of <20mmHg, and
- (2) a change in DBP of <10mmHg

(ii) the defined daily dose of antihypertensive medication being used is  $\leq 50\%$  of baseline

○ Absent clinical success

An absence of clinical success will be declared when neither partial nor complete clinical success can be declared.

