| 
11-Cmetomidate PET CT scan/Adrenal Vein sampling
 | 
 
• If patient is on a MR (spironolactone/eplerenone antagonist this will usually need to be stopped 6 weeks before going onto AVS sampling.
 
• Correct potassium depletion following local guidelines.
 
• Patient enrolled onto Ecrf with PET CT and AVS order of allocation determined by minimisation
 
 
Prior to 11-C-metomidate PET CT and [18F]CETO,PET CT scan:
 
 
• 0.5mg Dexamethasone to be taken 6hrly 3-5 days before scan
 
 
Prior to AVS:
 
 
• Spironolactone/eplerenone will usually be stopped 6 weeks before;
 
• Correct potassium depletion, following local guidelines. Bloods for ACTH, cortisol, electrolytes with bicarbonate, urea, creatinine, plasma renin mass and aldosterone
 
 
Treatment:
 
 
• 11-C metomidatePET CT scan and AVS results reviewed at specialist MDT 
 
○ If lateralisation occurs, patient informed and referred for adrenalectomy
 
○ Post-operative analyses of aldosterone-producing adenoma (genotyping and somatic mutations)
 
 
 
• All patients continue/commence treatment with spironolactone/eplerenone
 
 |

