## **10.0 Inclusion/Exclusion criteria:**

### **10.1 Inclusion Criteria**

- Male or female: Age >18 yrs.
- Diagnosis of PHA based on current published Endocrine Society consensus guidelines (Funder et al 2016)

- **Patients will be enrolled/consented when they have had each of the following:**

At least one paired measurement of plasma renin and aldosterone, measured off spironolactone/eplerenone and other polluting medications, showing an elevated ARR and.

1. *either* a plasma aldosterone >190 pmol/L after saline infusion
2. *or* 'spontaneous hypokalemia + plasma renin below detection levels + plasma aldosterone > 550 pmol/L)' (as per Endocrine Society guidance, 2016)
3. *or* failure to suppress plasma aldosterone by 30% + persistent PRA suppression after oral administration of captopril (as per Endocrine Society guidance, 2016)

**and** a CT or MRI scan of the adrenals with probable or definite adenoma(s) within the last five years

- Patients with elevated ARR can be put forward for consideration by the MDT as exceptional cases in whom spironolactone/eplerenone is not (fully) withdrawn, and/or saline suppression is not performed, IF:
  1. Plasma Aldosterone > 450 pmol/L **AND** plasma renin <0.5 pmol/ml/hr (<9 mU/L) if measured on treatment with ACEI (Lisinopril ≥20 mg or equivalent) or ARB (Losartan 100 mg or equivalent); OR

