**Biochemical success:**

○ Complete biochemical success

Complete biochemical success will be declared when both of the following occur:

- Serum potassium  $\geq 3.6$  mmol/l
- Normalisation of ARR ( $ARR_{\text{activity}} < 1000$  pmol/L per nmol/L/hr, if renin activity is recorded, otherwise  $ARR_{\text{mass}} < 91$  mIU/L)

○ Partial biochemical success

Partial biochemical success will be declared when the criteria for complete success are not met, and both of the following occur:

- Serum potassium  $\geq 3.6$  mmol/l
- $\geq 50\%$  reduction in serum aldosterone concentration

○ Absent biochemical success

An absence of biochemical success will be declared when neither partial nor complete clinical success can be declared.

In addition, a modified definition of clinical success (complete, partial, or absent) will be defined as follows:

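### Partial clinical success in SAP 1.9 mis-scores patients on no drugs at baseline, and can count an already controlled, unchanged patient as a success

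*Combined protocol and SAP*

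**What the plan says.** SAP 1.8.1 lists four primary outcomes tested in order: at least partial biochemical, complete biochemical, at least partial clinical and complete clinical success. SAP 2.3.1 analyses each in operated patients of the full analysis set. A test is right if it indicated unilateral disease and success followed, or if it did not and success did not follow. PET is non-inferior if the lower 95% limit of the paired difference in accuracy lies above -17%.

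SAP 1.9 defines clinical success as follows.

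- **Complete:** "Normalisation of BP, defined as SBP<135 and DBP<85 mmHg on home BP" (clinic 140/90 if there is no home reading), together with "Not taking any antihypertensive medications". Neither part refers to baseline.
- **Partial, route (a)**, whose heading requires that medication has not increased: BP "BP has reduced, or has normalised, since baseline", where a reduction is at least 20 mmHg systolic, or at least 10 mmHg diastolic with a systolic change under 20; and "the defined daily dose of antihypertensive medication being used is <150% of baseline".
- **Partial, route (b)**, headed "reduction in antihypertensive medication, with no increase in BP, i.e": systolic change under 20 mmHg, diastolic change under 10 mmHg, and a dose no more than half of baseline.

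No rule covers a baseline dose of zero or a baseline BP that is already normal. SAP section 3 leaves data rules to a separate specification. Protocol 10.1 and 10.2 set no minimum BP for entry.

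**The concern.** Success after surgery is the reference standard that decides which test was right. A patient scored as a success although nothing changed says nothing about unilateral disease, yet credits the test that sent the patient to surgery. If the two tests send unequal numbers to surgery alone, such false successes do not cancel out. A false failure does the reverse.

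The outcome affected, at least partial clinical success, is also a gate: complete clinical success counts as a primary analysis only if this one passes. Where the wording allows two readings, two programmers could score the same patient differently on a primary outcome.

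**Working it through.** No sample size or power figure in the plan depends on this definition, so there is no stated figure to reproduce. The check applies the SAP 1.9 rules literally to test patients.

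**Zero baseline dose.** Route (b) asks for follow-up dose ≤ 0.5 × baseline dose. At 0 to 0 this is 0 ≤ 0, true, although no medication was reduced. Route (a) asks for follow-up dose < 1.5 × baseline dose. At 0 to 0 this is 0 < 0, false, although no medication was added. Each result contradicts its route's own heading.

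**Normalised as a level or as a transition.** The level reading looks only at the 6-month value. The transition reading also requires an abnormal baseline.

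| | Home BP, baseline to 6 months | Daily doses | Level reading | Transition reading | After the fix |
|---|---|---|---|---|---|
| 1 | 130/80 to 130/80 | 3 to 3 | partial (a) | absent | absent |
| 2 | 130/80 to 130/80 | 3 to 4.4 | partial (a) | absent | absent |
| 3 | 150/90 to 150/90 | 0 to 0 | partial (b) | partial (b) | absent |
| 4 | 150/90 to 168/98 | 0 to 0 | partial (b) | partial (b) | absent |
| 5 | 180/105 to 150/92 | 0 to 0 | absent | absent | partial (a) |
| 6 | 180/105 to 150/92 | 2 to 2 | partial (a) | partial (a) | partial (a) |
| 7 | 180/105 to 130/80 | 0 to 0 | complete | complete | complete |
| 8 | 130/80 to 130/80 | 0 to 0 | complete | complete | complete |

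In row 2 the dose limit is 1.5 × 3 = 4.5, so 4.4 passes. Rows 5 and 6 have the same BP fall and differ only in whether drugs were taken. Under modified clinical success, which counts drug classes, row 3 is absent and row 5 is partial, so the zero-dose fault does not arise there. Row 1 stays ambiguous.

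**Weight of one patient.** In a patient operated on the strength of one test alone, success adds 1 to that test's correct count and failure adds 1 to the other's. Rescoring moves the paired difference by 2/n: 2/70 = 2.9 points (70 operated, Protocol 12.1 and 23.0) or 2/90 = 2.2 points (90, synopsis). Patients in whom both tests indicated the operated side do not move it.

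**Direction.** From the table in Protocol 33.0 and SAP 1.5, surgery on PET alone is C+D+G+H = 1+10+1+9 = 21% and on AVS alone I+J = 0.5+3.5 = 4%. False successes therefore lean toward PET. False failures such as row 5 lean the other way.

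**Illustrative size.** Assume the same true success rate r in every group, a share f of true failures scored as successes, concordant surgery K+L = 30%, and opposite-side cells omitted. The shift toward PET is 2 × (21 − 4) × (1 − r) × f / 55.

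| r | f = 5% | f = 20% |
|---|---|---|
| 30% | 2.2 points | 8.7 points |
| 50% | 1.5 | 6.2 |
| 70% | 0.9 | 3.7 |
| 90% | 0.3 | 1.2 |

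**Biochemical outcomes.** Complete success asks for potassium of at least 3.6 and "Normalisation of ARR", meaning a 6-month ARR below 1000 by renin activity, or below 91 by renin mass if activity is not recorded. Potassium may already be in range before surgery (synopsis, before the tests: "Correct potassium depletion following local guidelines"). The MDT exception in Protocol 10.1 admits aldosterone above 450 pmol/L with "plasma renin <0.5 pmol/ml/hr (<9 mU/L) if measured on treatment with ACEI" or an ARB. Its limiting ARR is 450/0.5 = 900, below 1000. By mass it is 450/9 = 50, below 91, taking the SAP's mass ratio as pmol per mIU. The standard routes ask for a raised ARR without giving a number.

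**The case against.** Several parts of the opposing case stand.

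- **Many criteria do require change.** Partial biochemical success needs a 50% fall in aldosterone, and the other legs of partial clinical success compare with baseline. A reader might infer that the success criteria as a whole describe only a state at 6 months; the text does not support that.
- **Route (a) refers to baseline and sits under a heading about a fall in BP.** The transition reading is fair. That makes the leg ambiguous rather than plainly wrong, but it still needs a rule.
- **The route headings show the intent at zero dose.** They do, but a program follows the inequality. Neither SAP section 3 nor the endpoints committee (Protocol 20.2) states a rule that overrides it.
- **An untreated patient with a large fall is not always a failure.** If BP falls below 135/85 the score is complete success (row 7). The failure in row 5 comes from a percentage of zero, not from defining success as a state.
- **The biochemical case is narrow.** An ARR of 900 is the corner of an exception route that still requires a raised ratio, with renin measured on an ACE inhibitor or ARB. Protocol 11.0 normally limits treatment before AVS to a calcium antagonist and doxazosin, so the entry value need not be the baseline value. One standard route also requires aldosterone above 550 pmol/L with undetectable renin.
- **Room for error may be small.** Since 17/2.86 = 5.95, a reader might infer that six flips could plausibly use up the margin. For ARR normalisation the planning table does not support that. Operated cells total 56%, and failures are C+G = 2% for PET alone and I = 0.5% for AVS alone. Among 70 operated that is 70 × 2/56 = 2.5 and 70 × 0.5/56 = 0.6 patients. Rescoring all of them moves the difference by (2.5 − 0.6) × 2.86 = 5.4 points. For clinical success, Protocol 4.3 expects at least half to be cured and the rest to need fewer drugs, which also suggests few failures, although fewer drugs is not the same as half the dose.

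**Conclusion.** The fault holds for partial clinical success, and so for the third primary outcome. The zero-dose mis-scoring follows from the text under either reading of normalised. The already controlled patient is a success or a failure depending on the reading, and the SAP does not choose.

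The effect on the comparison cannot be fixed from the documents, because they do not say how many operated patients will have a normal BP or no drugs at baseline. Under the assumptions above, false successes shift the difference toward PET by 0.3 to 8.7 points. That is a range over assumed inputs, not a forecast, and it takes no account of false failures, which offset it.

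For the biochemical outcomes the documents support less: a baseline ARR below the success limit is not ruled out, and on the planning table the effect is at most about 5.4 points with 70 operated. That justifies counting such patients and testing sensitivity to them. It does not justify rewriting the complete biochemical definition.

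**What to change.** Amend SAP 1.9 before the data are analysed.

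1. **Zero dose.** Route (b) requires a baseline dose above 0. In route (a), 0 to 0 counts as no increase.
2. **Normalised.** This counts only if baseline BP was at or above the same limit: systolic at least 135 or diastolic at least 85 mmHg on home readings, 140 or 90 on clinic readings. Put the matching systolic rule into modified clinical success. Its class-count logic already handles zero drugs and needs no change.
3. **Already met at baseline.** Keep the complete biochemical definition. Report how many operated patients met each success criterion at baseline, and repeat the primary comparison without them as a sensitivity analysis. This also covers the untreated patient with normal BP throughout (row 8), whom items 1 and 2 leave as a complete success.
4. **Source of baseline.** Protocol 9.2 keeps patients without a baseline visit in the analysis, so name screening values as the fallback where available.

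The cost is SAP wording and programming; no new data are needed. A few patients change category and success rates may fall slightly. An already controlled patient could then reach partial success only through a further BP fall or through route (b). The SAP must state where its rules depart from the published criteria it cites, which costs some comparability.

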**Biochemical success:**

○ Complete biochemical success

Complete biochemical success will be declared when both of the following occur:

- Serum potassium  $\geq 3.6$  mmol/l
- Normalisation of ARR ( $ARR_{\text{activity}} < 1000$  pmol/L per nmol/L/hr, if renin activity is recorded, otherwise  $ARR_{\text{mass}} < 91$  mIU/L)

○ Partial biochemical success

Partial biochemical success will be declared when the criteria for complete success are not met, and both of the following occur:

- Serum potassium  $\geq 3.6$  mmol/l
- $\geq 50\%$  reduction in serum aldosterone concentration

○ Absent biochemical success

An absence of biochemical success will be declared when neither partial nor complete clinical success can be declared.

In addition, a modified definition of clinical success (complete, partial, or absent) will be defined as follows:

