## 9.2 Study population

The potential constituency of patients at which MATCH is directed is the majority of all patients with PHA who indicate a desire to proceed to surgery if lateralisation can be confidently shown. The diagnostic criteria for PHA used in all participating centres will be drawn from the recently published updated Endocrine Society consensus guidelines (2016).(31) All patients will have had standard cross-sectional imaging by CT or MR scanning. If patients have had 11- C Metomidate scan and AVS with or without baseline visit they will be included in ITT analysis

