### **16.1 Screening and enrolment visit**

Informed Consent will be taken by physician or delegated to other members of the clinical research team. This will be taken following at least 24hrs of being in receipt of the patient information sheet. Demographic information will be recorded including gender, ethnicity, age, smoker, non-smoker, height weight. Medical history of cardiac, metabolic diseases and anything PI feels is related to hyperaldosteronism. Clinical examination. Concomitant hypertension medications will be recorded via class with a start and stop date where available.

During this visit the patient will have 3 blood pressures measured in the clinic following 5 minutes seated rest. Patients will be provided with a validated blood pressure monitor to measure home blood pressure. They will receive training on how to measure and record home blood pressures in blood pressure diary provided by a member of the clinical research team. This monitor will be used for clinic and home blood pressure measurements (Please see section above on Home blood pressure measurements)

A 12 lead electrocardiogram will be recorded. Followed by blood tests including electrolytes, , bicarbonate, creatinine, high troponin sensitivity test, brain natriuretic peptide (BNP), renin mass where available, renin activity, aldosterone and FBC. A serum HCG will be measured in child bearing potential females. Patients will be provided with x 1 24hr urine bottle for electrolytes which will be brought to baseline visit and a 10ml sample will be aliquoted for metabolomic analyses.

Inclusion and exclusion criteria will be checked with patient and recorded onto the eCRF. (Please see inclusion and exclusion criteria section 5.6)

Information and appointment details for 11C-metomidate PET CT scan and Adrenal Vein Procedures will be provided at this visit. The patient will then attend the PET CT scan and adrenal vein sampling procedures before next study visit , baseline visit.

**NB** Patients following review of PET CT scan and Adrenal Vein sampling procedure **who do not** meet the criteria for surgical intervention – adrenalectomy will attend for baseline visit, the post 2-week spironolactone /eplerenone 50mg and the post 2 week spironolactone 100mg visit. Following on from this they will have a follow-up study visit at 9-12 months. During this visit clinic blood pressures, 12 lead ECG,

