## **2. ANALYSIS POPULATIONS**

The “Enrolled Population” (EP) will consist of those who gave consent and met all inclusion/exclusion criteria.

The “Full Analysis Set” (FAS) will consist of those members of the EP who underwent both diagnostic tests (AVS and PET CT).

The “Substudy Population” (SP) will consist of those members of the EP who had one PET scan on spironolactone and one PET scan off spironolactone.

The numbers in each population will be reported. Reasons for exclusion from the FAS will be summarised. For those in the FAS, the numbers of participants who were randomised to each scan order, and who received the scans in each order, will be reported.

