## **2.3. EFFICACY OUTCOMES**

### **2.3.1. PRIMARY OUTCOMES**

The primary outcomes will be analysed hierarchically. If the first primary analysis is statistically significant at  $p < 0.05$ , then the second primary outcome will be analysed; if the second primary analysis is statistically significant at  $p < 0.05$ , then the second primary outcome will be analysed; and so on. If any primary analysis fails to reach  $p < 0.05$ , then subsequent analyses will be considered secondary analyses.

Each primary outcome will be analysed in the subgroup of FAS patients who undergo surgery.

- Cure of hypertension at 6 months (non-inferiority analyses)
  - comparing accuracy of AVS and 11C-Metomidate PET-CT
  - each scan judged to be accurate if it indicated unilateral disease and cure of hypertension was achieved after surgery, or if the scan did not indicate unilateral disease and cure was not achieved after surgery
  - report estimated difference in accuracy (Newcombe-Wilson method for paired data) between 11C-Metomidate PET-CT and AVS, with 95% CI
  - non inferiority of 11C-Metomidate PET-CT will be declared if the lower limit of the above 95% CI is greater than -17%
  - each measure of cure (see Section 1.8) will be analysed in turn
- Cure of hypertension at 6 months (superiority analyses)
  - in addition to above, report p-value from exact McNemar test
  - superiority of 11C-Metomidate PET-CT will be declared if  $p < 0.05$ , and the lower limit of the 95% CI is greater than 0%

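### SAP 1.9 defines absent biochemical success by the clinical scale, and its rules for absent success do not separate criteria not met from outcomes that could not be assessed

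*Combined protocol and SAP*

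**What the plan says.** SAP 1.9 sets out complete, partial and absent success on a biochemical, a clinical and a modified clinical scale. The biochemical section ends: "An absence of biochemical success will be declared when neither partial nor complete clinical success can be declared". The clinical section ends: "An absence of clinical success will be declared when neither partial nor complete clinical success can be declared". The modified clinical section likewise refers to its own scale.

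SAP 1.8.1 lists four primary outcomes in hierarchical order: at least partial biochemical, complete biochemical, at least partial clinical, and complete clinical success. SAP 1.8.2 has three-level biochemical and clinical success as secondary outcomes.

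On the analysis set, SAP 2.3.1 says: "Each primary outcome will be analysed in the subgroup of FAS patients who undergo surgery". The full analysis set (SAP section 2) requires that both tests were done; it does not require outcome data. Protocol 9.2 says of patients who had both tests that "with or without baseline visit they will be included in ITT analysis". On scoring, SAP 2.3.1 counts a test as accurate if it indicated unilateral disease and cure followed, "or if the scan did not indicate unilateral disease and cure was not achieved after surgery".

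The SAP has several provisions for missing values:
- 1.8 substitutes a later visit up to 12 months, then the closest earlier one.
- 1.9 uses clinic BP where home BP is missing, and renin mass where renin activity is missing.
- 1.10.2 allows carry-forward of follow-up values for selected analyses that it does not name.
- Section 3 leaves imputation rules to a separate validation plan.
- The only planned sensitivity analysis (2.3.6) excludes AVS technical failures.

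**The concern.** There are two faults. The first is that the absent category on the biochemical scale is decided by blood pressure and drug use. The three biochemical categories are then neither exclusive nor exhaustive.

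The second is that a category defined by what cannot be declared takes in two kinds of patient: those measured who failed the criteria, and those for whom the criteria cannot be evaluated. In most responder analyses, moving the second group into failure lowers both rates. Here it does more, because a non-cure counts as a correct call for whichever test did not indicate unilateral disease. A patient operated on because of PET-CT alone, with no assessable outcome, would become evidence for AVS, and the reverse for AVS alone. The two groups are expected to differ greatly in size, so the effect would not cancel. Superiority of PET-CT is the SAP's stated primary objective (1.2.1), and that comparison is the exposed one.

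**Working it through.** **1. The biochemical categories read literally**

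| Biochemical criteria | Clinical success | Category under the printed rule |
|---|---|---|
| Complete | None | Complete and absent |
| Partial | None | Partial and absent |
| Not met | Partial or complete | No category |
| Not met | None | Absent |

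Only the last row is classified as intended. If at least partial biochemical success were programmed as not absent, it would equal at least partial clinical success, so the first and third primary outcomes would coincide. If it is programmed from the positive criteria, the slip does not reach the primary analysis.

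**2. What each outcome needs**
- Complete biochemical success: follow-up potassium and ARR.
- Complete clinical success: follow-up BP and drug status.
- Partial biochemical success: also baseline aldosterone.
- Partial clinical success: also baseline BP, and defined daily dose at both times.

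The fallbacks replace follow-up values or swap one measurement for another. None replaces a missing baseline. What remains is operated patients with no usable post-surgery value (all four outcomes) and those with no baseline BP, aldosterone or dose (the two at-least-partial outcomes only, and only where complete success was not reached).

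**3. The plan's own figure**

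Inputs are the cell percentages in protocol section 33.0, repeated in SAP 1.5.
- D+H+I+O+Q = 10+9+0.5+0.25+0.25 = 20.
- G+J+M+P = 1+3.5+0.25+0.25 = 5.
- p = 20/25 = 80%, as stated.

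**4. Paired difference under SAP 2.3.1, complete data**
- Operated: C+D+G+H+I+J+K+L+M+O+P+Q = 56.
- PET-CT alone: C+D+G+H = 21. AVS alone: I+J = 4. Both, same side: K+L = 30. Opposite sides: 1.
- PET-CT accurate: D+H+I+L+O+Q = 49, and 49/56 = 87.5%.
- AVS accurate: C+G+J+L+M+P = 35, and 35/56 = 62.5%.
- Difference: 14/56 = +25.0 points.

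Cell C is credited to AVS because AVS did not indicate unilateral disease and cure failed. The protocol formula omits C, which gives 34/56 = 60.7% and a difference of +26.8. Opposite-side cells follow the protocol formula and net to zero.

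**5. A share m of operated outcomes missing at random**

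*Scored absent:*
- Only PET-CT right: 20(1−m) + 4m.
- Only AVS right: 6(1−m) + 21m.
- Difference: (14 − 31m)/56.

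| m | Difference (points) |
|---|---|
| 0 | +25.0 |
| 5% | +22.2 |
| 10% | +19.5 |
| 20% | +13.9 |

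*Scored success:* the difference is [14(1−m) + 21m − 4m]/56 = (14 + 3m)/56, or +25.5 at 10%.

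*Excluded:* it stays at +25.0, given missing at random.

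**6. In patients**

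Protocol section 23.0 expects 70 operations. Seven missing outcomes scored absent would credit AVS with 7×21/56 = 2.6 and PET-CT with 7×4/56 = 0.5. Another 7×30/56 = 3.75, concordant on the same side, would count against both tests and leave the difference unchanged. One cured patient operated on PET-CT alone and scored absent moves the difference by 2/70 = 2.9 points.

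**7. Power with 70 operated**

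This is a simulation with 6,000 runs, using the Newcombe paired 95% CI and the exact McNemar test.

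| m | Superiority, scored absent | Superiority, excluded |
|---|---|---|
| 5% | 75% | 82% |
| 10% | 60% | 82% |
| 20% | 34% | 75% |

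Non-inferiority power at the −17% margin is at least 97% in every case.

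**The case against.** A reader might infer that the SAP scores missing outcomes as failed cures. It does not say so. The wording is the usual form for the last level of a three-level scale. SAP 1.10.2 has categorical data reported with counts of missing values, which implies that missing categories are expected, and section 3 places imputation in a document not available here. This stands: scoring missing as failure is one reading of the text.

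A reader might also infer that the biochemical slip undermines all four primary outcomes. Two of them are clinical and do not use that line. The two biochemical ones can be derived from the positive criteria.

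A third tempting inference is that doses are not collected, because protocol 16.1 says "Concomitant hypertension medications will be recorded via class with a start and stop date where available". That sentence does not exclude dose. The SAP lists defined daily doses at screening, baseline and each later visit it summarises, and makes their change a secondary outcome. The texts need reconciling, but no missing data item is shown.

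On size, the table's outcome is normalisation of renin and ARR, which needs no baseline value. Step 5 therefore represents missing post-surgery outcomes, and missing baselines alone would do less. The protocol's 10% is a share of recruits, and some of those would never reach surgery. Operated patients also have several visits from which to substitute. All of this stands, so the figures are illustrative.

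The objection does not close the gap. No fallback supplies a missing baseline, patients without a baseline visit are kept, and the SAP does not say how an unassessable patient enters the accuracy comparison.

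**Conclusion.** The biochemical rule is wrong as printed. It certainly affects the three-level secondary outcome. Whether it affects the first primary outcome, which gates the hierarchy, depends on how that outcome is programmed.

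The residual wording is an ambiguity and not a stated missing-equals-failure rule. Its consequence would have a direction, though. Under the planning table, scoring unassessable patients as absent works against PET-CT by 25.0 − 19.5 = 5.5 points at 10% missing, and superiority power would be 60% against 82% with exclusion. Non-inferiority is barely touched.

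These sizes assume the planning-table frequencies, 70 operations, missingness at random among operated patients, and literal use of the absent rule. The documents give no rate of unassessable outcomes after surgery.

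**What to change.** 1. In SAP 1.9, change clinical to biochemical in the absent-biochemical rule. State that at least partial and complete success are derived from the positive criteria.
2. On all three scales, define absent as: the components needed to rule out complete and partial success were measured, and the criteria were not met. Otherwise the outcome is not assessable. Apply this outcome by outcome. For example, potassium below the SAP's 3.6 mmol/l threshold settles the biochemical result without a baseline, and a missing baseline does not make complete success unassessable.
3. In SAP 2.3.1, state that a not-assessable patient is credited to neither test and is left out of the paired analysis for that outcome. Report the numbers by which test indicated surgery.
4. In SAP 2.3.6, add two sensitivity analyses: all not-assessable outcomes scored as success, and all scored as failure.
5. Reconcile protocol 16.1 (recording by class) with the SAP's defined daily doses. The documents do not show that a new data field is needed.

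The cost is a few lines of SAP text and one extra table before database lock. The drawback is slightly fewer patients in the primary paired analysis. Exclusion is unbiased only if outcomes are missing at random, which is why both extreme scorings are needed.
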